### Compensation

All participants will receive compensation for their participations, which will be graduated based on phases’ completion for a maximum of 60 euros for each participant. Compensations will be divided as follows:

drop-out after baseline: €5;drop-out after follow-up 1: €15;drop-out after follow-up 2: €30;drop-out after follow-up 3: €40;drop-out after follow-up 4: €50;completion of follow-up 5: €60.

This procedure is considered important to maximize motivations and to reduce the risk of drop-outs.

All participants will receive, at the end of the study, the following informative materials: the pdf materials of the fifth intervention session on infant’s and postpartum sleep; a pdf containing information on children sleep from 0 to 5 years.

### Ethical aspects

The trial was approved by the by Ethics Committee for psychological studies of the Guglielmo Marconi University of Rome, Italy (Approval letter: 19.02.2024) and the Bioethics Committee of the University of Bologna, Italy (ID: 0388063).

In case of important protocol modifications, amendments will be submitted for approval by the Ethics Committee for psychological studies of the Guglielmo Marconi University and the Bioethics Committee of the University of Bologna. The trial protocol registered with Clinicaltrials.gov will be updated accordingly.

Participants’ data will be maintained in secure spaces accessible only by the investigators. Signed informed consents and salivary samples will be stored in secure rooms at the study sites for the duration of the study. All study data will be entered in a database, labelled with the ID-codes. Only the study investigators will have access to the database.

### Statistical analysis

Analyses will be performed by a professional biostatistician ([name]). For all outcomes, intent-to-treat analyses (ITT) will be performed including all randomized women in the statistical analyses. Descriptive statics will be reported, including recruitment rate, dropout rate, and data completion rate. A detailed flow chart of study participants will be provided. Only data from those completing the trail will be analysed. Baseline characteristics of non-completers and completers will be compared. Independent t-test and Chi-square test will be conducted to compare randomized groups on baseline characteristics. Significant differences between dropouts and retained participants will be investigated with comparisons on baseline and outcome characteristics. Multivariate linear regressions will be used for testing associations with insomnia during pregnancy and postpartum depression. A multivariate mixed effects model analysis will be performed to test the interventions efficacy over time. Within- and between-groups differences will be measured including as factors the Group (A, B1, B2) and TIME (Pre-; Post-; last weeks of pregnancy; Birth; 3; 6) and as outcome all endpoints which will be collected at all assessments. For all analyses statistical significance is set at p-values < 0.05.

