### Sample size

To estimate required sample size for adequate power of the clinical trial, we used as primary outcome peripartum depression (PDS) at post-treatment. A study that compared scores on the Edinburgh Postnatal Depression Scale (EPDS) in 132 women divided into two groups, cognitive-behavioral therapy for insomnia (*N* = 89) or control group (*N* = 43), before, during and after pregnancy [35] was used. The software G-Power was used to estimate sample size: 114 women in total would be needed to have an effect power of at least 80%. Drop-out rates in previous studies were around 5 to 16% for post-treatment and short follow-ups [28, 33] and around 17% for 6 months follow-up [36]. We plan to recruit 150 participants, accounting for a dropout rate of 24%.

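### The Statistical analysis section fixes two incompatible analysis sets: all randomised women, and trial completers only

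*Protocol article*

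**What the plan says.** Everything that creates the conflict stands in one paragraph of the protocol article, under Statistical analysis.

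- The first rule: "For all outcomes, intent-to-treat analyses (ITT) will be performed including all randomized women in the statistical analyses".
- The second rule, three sentences later: "Only data from those completing the trail will be analysed" (the context shows that the trial is meant). It is not called per-protocol, supportive or sensitivity.
- Next comes "Baseline characteristics of non-completers and completers will be compared", and later a comparison of dropouts with retained women on baseline and outcome characteristics.
- For efficacy: "A multivariate mixed effects model analysis will be performed to test the interventions efficacy over time", with Group (A, B1, B2) and time as factors.

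Under Sample size, the planning outcome is depression at post-treatment. The article says "114 women in total would be needed to have an effect power of at least 80" per cent, and then "We plan to recruit 150 participants, accounting for a dropout rate of 24" per cent. It cites earlier dropout of about 5 to 16% at post-treatment and short follow-up, and about 17% at six months.

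The primary hypotheses also concern post-treatment, which is follow-up 1, six weeks after baseline. The last assessment is follow-up 5, six months after birth. The Compensation section classes women who leave after any of follow-ups 1 to 4 as drop-outs and reserves completion for follow-up 5.

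**The concern.** The two rules define different populations for every efficacy estimate. A later analysis plan that chose either would contradict the published article. If the choice were made once data had been seen, the analysis set would be a post hoc decision.

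The completer rule carries the risk. Completing is an event after randomisation, and the arms differ in ways that could affect it. B2 has a weekly chat with a clinician that includes adherence strategies, B1 has no chat, and the article's discussion expects this contact to raise adherence. Restricting the comparison to women who stayed gives up the protection of randomisation. It could also discard follow-up 1 measurements already collected (EPDS, ISI, actigraphy and, where consented, cortisol) because a woman left months later.

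**Working it through.** **1. The plan's own figure.** Inputs from Sample size: 114 women needed, 24% dropout.

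114 / (1 − 0.24) = 150, which matches the recruitment target. Conversely 150 × 0.76 = 114. The stated 80% power is therefore attached to the women remaining after dropout. The 114 itself cannot be reproduced, because no effect size, standard deviation or test is given.

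**2. How far the two sets differ.** Overall, 150 − 114 = 36 women. If the 150 are split 1:1:1 (an assumption), 100 are randomised, 50 per arm. Intention-to-treat keeps 100. Completers-only keeps 100 × 0.76 = 76, or 38 per arm.

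**3. Women with follow-up 1 data who would still be removed.** This takes completion to mean reaching follow-up 5. The number per 100 randomised is final dropout minus dropout at post-treatment.

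| Final dropout | 5% lost by post-treatment | 16% lost by post-treatment |
|---|---|---|
| 24% (planning allowance) | 24 − 5 = 19 | 24 − 16 = 8 |
| 17% (cited for six months) | 17 − 5 = 12 | 17 − 16 = 1 |

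**4. Power.** Assumptions: t-test, two-sided 5% (the article gives 0.05 without sidedness), 50 randomised per arm, and d about 0.65, back-solved as the effect that 38 per arm detects with 80% power.

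| Women analysed per arm | Power |
|---|---|
| 38 (completers, 50 × 0.76) | 0.80 |
| 42 (observed at follow-up 1, 50 × 0.84) | 0.84 |
| 47.5 (observed at follow-up 1, 50 × 0.95) | 0.88 |
| 50 (no loss at all) | 0.90 |

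The fair comparison is 0.80 against 0.84 to 0.88, since women lost before follow-up 1 have no post-treatment outcome under either rule.

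**5. Bias, for illustration only.** Suppose 24% drop out of each arm, B1 dropout is uninformative, and B2 dropouts do D standard deviations worse than B2 completers. The completers' contrast then shifts by 0.24 × D towards benefit. The standard error at 38 per arm is √(2/38) = 0.229 SD. Under no true effect, the two-sided rejection rate is P(Z > 1.96 − shift/SE) + P(Z < −1.96 − shift/SE).

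| D (SD) | Shift (SD) | Rejection rate under no effect |
|---|---|---|
| 0.25 | 0.06 | 0.058 |
| 0.5 | 0.12 | 0.082 |
| 1.0 | 0.24 | 0.18 |

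If dropout is equal and equally informative in both arms, the shift is zero. The document supports none of these values of D over another.

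**The case against.** The strongest reply is that the intention-to-treat sentence is explicit and covers all outcomes, while the completer sentence follows remarks on recruitment, dropout and the flow chart and may be loose drafting. The planned comparison of dropouts with retained women on outcome characteristics suggests that some of the dropouts' outcome data will be used. This stands to the extent that nobody can say the completer rule governs. It does not remove the conflict, because the sentence is unqualified.

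Three stronger readings are tempting, and the document does not support them:

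- **That the efficacy result will be a completers-only comparison.** Nothing ranks the two sentences, so this consequence is conditional.
- **That completion is defined as follow-up 5.** The article gives no definition. The Compensation section makes it the natural reading, but it remains an inference.
- **That power falls from 80% to about 68%.** That figure comes from attaching the 80% to all randomised women, for example 38 per arm falling to 29 at d = 0.65. Sample size attaches it to the 114 left after dropout. The figure also charges the rule with women lost before follow-up 1. Whether 38 per arm is the number randomised or the number evaluable is a separate question about the 150 and the 114.

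It is also fair to say that the article reports no differential dropout. Exposure to bias is shown; an actual bias is not.

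**Conclusion.** The point holds as a contradiction in current text that leaves the efficacy population undefined. It is not a detail left to an analysis plan, since the article itself states both rules, and it should be corrected before analysis.

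If the completer sentence governs, the randomised comparison is exposed to attrition bias of unknown size and direction, possibly zero. If completion also means follow-up 5, about 8 to 19 per 100 randomised women (24% final dropout) or 1 to 12 per 100 (17%) would be dropped despite having post-treatment data. These ranges assume that the cited 5 to 16% early loss applies to this trial. The power forgone is modest, about 0.80 instead of 0.84 to 0.88, and depends on the assumed 50 per arm and the back-solved d. It is not a shortfall from the stated power. The case rests on the undefined population and the bias exposure, not on power.

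**What to change.** Delete the completer sentence, or label it a sensitivity analysis and say which assessment counts as completion.

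State that the primary efficacy analysis includes all women randomised to B1 and B2, in the arm assigned, using every available assessment in the planned mixed effects model. A likelihood-based fit can use partial follow-up, so no woman need be excluded for leaving later. Group A may stay in the model as the non-randomised comparator. Keep the comparison of completers with non-completers as description.

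The cost is a change to one or two sentences, submitted through the amendment route already described under Ethical aspects, with the registry entry updated. It needs no new data, no extra participants and no new model.

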## Methods

### Study design

Randomized controlled trial with three parallel arms (intervention, active control group, passive control group) with allocation ration 1:1 and 5 follow-up assessments following pregnant women from early pregnancy (within the 15° gestational week) to 6-months after birth. Three of the six phases of the study (Baseline, follow-up1 and follow-up5) will also include Ecological Momentary Assessment (EMA).

The protocol follows the Standard Protocol Items: Recommendations for Interventional Trials (SPIRIT) statement (see SPIRIT checklist available as Supplementary File S1).

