### Randomization

Participants in Group B will be randomly assigned to one of the following two subgroups:

*Subgroup B1* (active control): psychological placebo (*N* = 38);

*Subgroup B2* (intervention): psychoeducation based on CBT-I adapted to pregnancy (*N* = 38).

Allocation concealment will be performed in steps: firstly, a code has to be created for each future participants to set the online platform they will use. The alphanumeric code (here referred to as “ID-code”) is composed of a string of numbers and the subgroup (B1 or B2). The ID-codes will be created before the start of the study by a computerized generator of random numbers. Each participant, upon allocation, will receive a folder with their ID-code, together with the instruments and information for the baseline phase (see below). A member of the research team who will not conduct screening and assignment to groups will prepare the sealed folders containing the ID-codes. The folders of Group B will be shuffled and then sequentially numbered. After the screening, each participant entering the study in the Group B will be given a numbered folder labelled with the letter “B”. With this procedure, participants will be randomly assigned to subgroup B1 or B2, concealing allocation to both participants and the investigator. Neither the psychologists conducting the screening interviews, nor the participants will know the allocation until after the screening.

Participants in the passive control condition (*Group A*) will also receive a randomly generated ID-code.

Participants will be given the credentials to log-in to their personal area on the website of the study for the next phases. The credentials will match the ID-code and thus each condition will have access to the respective online contents. The ID-codes will be used for each subsequent phase of the study.

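### The planned B1 v B2 baseline significance tests are uninformative, and adjusting B2 minus B1 for the outcome's own baseline value would add precision at almost no cost

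*Protocol article*

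**What the plan says.** All in the protocol article:

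- Statistical analysis, on baseline: "Independent t-test and Chi-square test will be conducted to compare randomized groups on baseline characteristics". The section does not say what follows from the result of these tests.
- Statistical analysis, on efficacy: a mixed effects model, in which "Within- and between-groups differences will be measured including as factors the Group (A, B1, B2) and TIME". The first of the six TIME levels is the pre-treatment assessment. No baseline covariate is named.
- Statistical analysis, on the threshold: "For all analyses statistical significance is set at p-values < 0.05".
- Randomization: Group B is split at random into B1 (placebo content) and B2 (intervention), 38 women each, using sealed, shuffled and numbered folders so that allocation is concealed. Group A is not randomised.
- Sample size: 114 women are needed for at least 80% power, and 150 are to be recruited to allow for 24% dropout.

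**The concern.** There are two linked points.

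First, a significance test of baseline differences between randomised arms tests a null hypothesis that is true by design. A significant result is a chance finding. A non-significant one, with arms this small, leaves room for an observed imbalance large enough to matter. Printed beside the baseline table, such p-values invite a reader to take p > 0.05 as evidence of balance.

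Second, the step that does deal with chance imbalance is to adjust the treatment contrast for the baseline value, and the stated model does not clearly do so. It treats the pre-treatment measurement as one more outcome level. With a separate pre-treatment mean in each arm, the contrast at a later visit subtracts the whole baseline difference, although only the fraction r of it is expected to persist. The estimate is then over-corrected in any trial with an imbalance, and its variance is larger than it need be. At stake is precision in a trial with small randomised arms, from data that will be collected anyway.

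**Working it through.** **Inputs from the protocol article.** 38 per randomised arm (Randomization); 114 needed, 150 recruited, 24% dropout (Sample size); threshold 0.05 (Statistical analysis; two-sided assumed, as sidedness is not stated).

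**Assumptions, not in the document.** r = 0.3, 0.5 or 0.7; a true effect of 0.65 SD at post-treatment, which is about what a two-sample t-test detects with 80% power at 38 per arm; equal outcome SD before and after treatment; complete data.

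**The plan's own figure.** 114 / (1 − 0.24) = 150, which reproduces. The 114 cannot be rebuilt, because no effect size, SD or test is given.

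**Arm sizes.** 38 as stated; 150/3 = 50 if the recruited total is split equally over A, B1 and B2; 38 × 0.76 = 28.9, so 29, if only 38 are randomised and only completers are used.

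**1. Smallest observed baseline difference that reaches p < 0.05.** In SD units this is t(0.975, 2n−2) × √(2/n).

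- n = 38: 1.993 × 0.2294 = 0.457
- n = 50: 1.984 × 0.2000 = 0.397
- n = 29: 2.003 × 0.2626 = 0.526

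An observed imbalance of 0.4 SD is therefore not flagged at 38 or 29 per arm, and sits at the threshold at 50.

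**2. What the stated model estimates.** With separate pre-treatment means and complete data, the group-by-time contrast at post-treatment is (B2 post − B2 pre) − (B1 post − B1 pre). Given an observed baseline imbalance D, the expected post-treatment difference with no effect is rD, so the contrast is shifted by rD − D = −(1−r)D. For D = 0.4 SD the size of the shift is:

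- r = 0.3: 0.7 × 0.4 = 0.28 SD
- r = 0.5: 0.5 × 0.4 = 0.20 SD
- r = 0.7: 0.3 × 0.4 = 0.12 SD

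Averaged over randomisations D is zero, and so is the shift.

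**3. Variance.** In units of the outcome variance, the change score has 2(1−r) and the baseline-adjusted outcome has 1−r². The ratio is (1−r)(1+r) / [2(1−r)] = (1+r)/2, which is 0.65, 0.75 and 0.85 at r = 0.3, 0.5 and 0.7.

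**4. Power at 0.65 SD.** Two-sided t-test (noncentral t), with standardised effect 0.65/√[2(1−r)] for the change score and 0.65/√(1−r²) for the adjusted contrast. At 38 per arm the standardised effects are 0.549 and 0.681 (r = 0.3), 0.650 and 0.751 (r = 0.5), and 0.839 and 0.910 (r = 0.7).

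| Per arm | r = 0.3 | r = 0.5 | r = 0.7 |
|---|---|---|---|
| 38 | 66% to 83% | 80% to 90% | 95% to 97% |
| 29 | 54% to 72% | 68% to 80% | 88% to 93% |
| 50 | 78% to 92% | 90% to 96% | 99% to 99% |

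Each cell runs from change score to baseline-adjusted. The gain is largest when r is low and has all but vanished at 50 per arm with r = 0.7.

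**The case against.** The strongest reply is that nothing here is wrong. The pre-treatment value is already in the model as a level of TIME. That is a recognised analysis, unbiased over randomisation, and the shift in step 2 exists only conditional on an imbalance that may not occur. The article states no interaction term, covariance structure or baseline constraint, and a full analysis plan may set these and list covariates.

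Much of this stands. It makes the point one of efficiency and conditional bias. It makes the change-score reading depend on each arm having its own pre-treatment mean. It also means that the absence of other covariates, such as baseline ISI or site, is no finding. It does not dispose of the baseline tests, which the article states outright, or of its stated handling of the pre-treatment value as an outcome level.

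Two stronger readings are tempting and are not supported:

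- *That the tests decide comparability, or whether to adjust.* No sentence says that a non-significant test establishes balance or makes any adjustment depend on p.
- *That the tests would miss a 0.5 SD difference with some stated probability.* A t-test has a type II error of 42% at 38 per arm, 54% at 29 and 30% at 50, but for a true population difference, which is zero between concealed randomised arms. An imbalance of 0.5 SD actually observed would be flagged at 38 per arm (p = 0.032) and at 50 (p = 0.014). These rates do not describe chi-square tests either.

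**Conclusion.** The point holds as a free improvement. The baseline tests of B1 against B2 inform nothing and should go. The stated model, read with a separate pre-treatment mean per arm, gives up precision: baseline adjustment would cut the variance of B2 minus B1 by 35%, 25% or 15% at r = 0.3, 0.5 or 0.7. At 38 per arm and an assumed 0.65 SD effect, that is a gain of about 17, 10 or 2 percentage points of power. Adjustment also removes the conditional shift of (1−r) times any chance imbalance.

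These sizes rest on r and an effect that the document does not give, on equal SDs before and after treatment, and on complete data. A reader might infer that the planned treatment estimate is biased. It is not biased over repeated randomisation, only shifted in a trial that happens to be imbalanced.

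**What to change.** In Statistical analysis, replace the baseline tests of the randomised groups with a descriptive table of B1 and B2 (means and SDs, or counts and percentages) without p-values. Then add one sentence on the efficacy model: for every outcome measured at baseline, B2 minus B1 is adjusted for that outcome's own baseline value, either as a covariate or through one baseline mean common to B1 and B2, whatever the observed baseline difference. Group A keeps its own baseline mean, since it is not randomised. Outcomes first measured after birth, such as parenting stress and infant sleep, are outside the rule.

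The cost is a change of wording and about one degree of freedom. No further data are needed.

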### Screening

Following our recruitment strategy, all women at the first ultrasound check or all women expressing interest through the study’s website will be contacted for an appointment with a clinical psychologist for the screening, which will be conducted in a confidential space in a room at the Universities’ Department involved (Department of Biomedical and Neuromotor Sciences, University of Bologna; Department of Human Sciences, Guglielmo Marconi University of Rome). This space will be used for all in-person contact with the participants (detailed below). Study’s materials, including biological samples, will all be conserved labelled with pseudonymized codes (number and letters without personal information) in a secured room in the Department of Biomedical and Neuromotor Sciences, University of Bologna for the duration of the study. A member of the research team will explain study aims and procedure. All women will be asked to read and sign the informed consent before proceeding. A separate informed consent will be asked for the use of salivary samples for the analyses of cortisol level and DNA-methylation (see “Baseline” section). Screening will be evaluated through a psychological structured interview (Structured Clinical Interview for DSM-5, SCID-5 in the brief version QuickSCID-5) [37] and a specific interview about their sleep [38] by clinical psychologists ([name], [name], [name]). Information on pregnancy and socioeconomic variables will be collected. Women will be asked to share along with their consent, gynaecological medical data on their health status (e.g. information on pregnancy).

Eligible participants will be divided in two groups:*Group A*: control group of healthy pregnant women with no insomnia complaints (*N* = 38);*Group B*: pregnant women complaining of subthreshold or clinical insomnia (*N* = 76).

Insomnia categories (absence of insomnia; subthreshold insomnia; clinical insomnia) will be operationalized using the validated questionnaire ‘Insomnia Severity Index’ (ISI) [39]. ISI is a measure of insomnia severity in the 2 weeks before compilation. Participants provide answers on a five-point Likert scale on 7 items. The score is the simple sum of the answers to all the questions and can range from 0 to 28. The total score is interpreted as follows: no insomnia (0–7); subthreshold insomnia [8–14]; clinical insomnia [15–28].

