Group A (passive control group) will serve as a comparator for the absence of any intervention, accounting for natural changes in sleep during pregnancy.

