### Intervention

*Group A* (ISI score under 8) will be observed longitudinally through standard of care above-described procedure, without an active intervention. *Group B* (ISI score above 7) will be randomly assigned to 2 active interventions both conducted through digital therapy: (1) psychoeducation based on CBT-I adapted for pregnancy (experimental intervention; subgroup B2); (2) information on sleep disorders and on peripartum-related issues (placebo intervention; subgroup B1).

Each intervention will share the following characteristics:

fully digitalized on the study website;composed of 6 weekly 20-minutes online sessions;each session will include a before and after brief survey to monitor satisfaction;each participant will start the intervention upon completion of the baseline assessment;participants will be asked to fill out directly on the website a reduced version of the sleep and emotion diaries each day during the intervention (6 weeks).

For Group B1 (placebo), each session will include: educational videos (ca. 20 min) on aspects related to pregnancy and sleep; brief feedback questions. Participants in the placebo intervention will not be given specific indications on skills or techniques for sleep difficulties and will not have access to the weekly chat with the clinician.

Sessions will cover the following contents:

Session 1: phases of pregnancy;Session 2: sleep disorders;Session 3: nutrition and physical activity during pregnancy;Session 4: childbirth;Session 5: psychophysical development of the child in the first year of life;Session 6: synthesis of previous sessions.

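### The efficacy model's Group factor includes the non-randomised, low-ISI Group A, and the test is not tied to the randomised B2-versus-B1 comparison

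*Protocol article*

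**What the plan says.** The Statistical analysis section names the model and its purpose: "A multivariate mixed effects model analysis will be performed to test the interventions efficacy over time". It then gives the factors: "Within- and between-groups differences will be measured including as factors the Group (A, B1, B2) and TIME", with six time levels from pre-treatment to six months. The threshold is common to everything: "For all analyses statistical significance is set at p-values < 0.05". The same section promises intention-to-treat analysis of the randomised women.

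Study design describes the trial as "Randomized controlled trial with three parallel arms (intervention, active control group, passive control group) with allocation ration 1:1". Randomization is narrower: "Participants in Group B will be randomly assigned to one of the following two subgroups". Intervention agrees that Group B "will be randomly assigned to 2 active interventions both conducted through digital therapy". Screening and Intervention form Group A from women with ISI 0–7 and Group B from women with ISI 8–28, and ISI total is listed among the primary outcomes. Screening gives Group A its role: it "will serve as a comparator for the absence of any intervention, accounting for natural changes in sleep during pregnancy".

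The primary hypothesis compares the intervention group with the control group at post-treatment. The expected-results section makes clear that this means the placebo group, B1.

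**The concern.** A three-level Group factor crossed with TIME asks whether any of the three trajectories differ. One of the three groups was selected for low values of an outcome under test, so its trajectory can differ from the other two for reasons unrelated to treatment. When a noisy score is cut at a threshold and measured again, the low group tends to drift up and the high group down. Within-group tests in B2 pick up the same downward drift.

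Group A may also follow a genuinely different course through pregnancy and after birth, which would again make the interaction significant with B1 identical to B2.

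The wording does little to prevent misreading. Screening calls Group A a "control group of healthy pregnant women with no insomnia complaints", so the control group of the primary hypothesis is unambiguous only once the expected-results section is read. Calling A one of three randomised 1:1 arms gives an A-versus-B comparison a standing it does not have. The dissemination plan makes approaches to medical services depend on a positive efficacy result, so which test decides that matters.

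**Working it through.** **1. The plan's own numbers.** The groups are 38 + 38 + 38 = 114, and 114 / (1 − 0.24) = 150, which reproduces the recruitment target. Of the 114, the randomised comparison uses 38 + 38 = 76.

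**2. Expected drift with no treatment effect.** From the article: the cut between ISI 7 and 8, and 38 per group. Assumed, because the article gives no values: ISI normal with mean μ and SD σ, correlation r between the two measurements, no population change, and the screening score serving as baseline. With z = (7.5 − μ)/σ:

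- change in A = (1 − r)·σ·φ(z)/Φ(z)
- change in B = −(1 − r)·σ·φ(z)/(1 − Φ(z))

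For μ = 9 and σ = 5, z = −0.30, φ = 0.381 and Φ = 0.382. A changes by 5 × 0.998 × (1 − r) = 4.99(1 − r), and B by −5 × 0.617 × (1 − r) = −3.09(1 − r). At r = 0.6, 0.7 and 0.8 this gives A +2.0, +1.5, +1.0 and B −1.2, −0.9, −0.6 points.

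**3. Null rejection rates.** Trials were simulated with B1 and B2 identical, 38 per group, at two-sided 5%. The three-group F test on pre–post change equals the Group×Time test with two time points. It was set beside the B2-versus-B1 t-test on change.

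| How baseline ISI is obtained | Correlation | Three-group test rejects |
|---|---|---|
| Same score as screening (mean 7 or 9, SD 5) | 0.5 | 99% |
| Same | 0.6 | 95–96% |
| Same | 0.7 | 84–88% |
| Same | 0.8 | 63–71% |
| Same | 0.9 | 38–39% |
| Separate, correlation decaying with time (mean 8, SD 5) | 0.5–0.9 | 30–48% |
| Separate, constant correlation (mean 8, SD 5) | 0.5–0.9 | 4–5% |

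Where the same score is used at r = 0.6–0.8, the range covers a continuous version (mean 9, 3,000 runs: 95%, 84%, 63%) and a version rounded to the 0–28 scale (2,000 runs per setting). The B2-versus-B1 test rejected in 4.2–5.6% of trials in every setting where it was run.

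**4. Which row applies.** The article does not say. The outcome list gives ISI at baseline and follow-ups 1–5 with no separate screening score, which fits the same-score rows. The Baseline section has questionnaires completed on the website after enrolment, which fits a second measurement.

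**5. Baseline as covariate.** For the B2−B1 difference, the ratio of covariate-adjusted variance to change-score variance is σ²(1 − r²) / [2σ²(1 − r)] = (1 + r)/2. At r = 0.5 this is 0.75 (25% less), and at r = 0.6 it is 0.80 (20% less).

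**The case against.** The strongest reply is that the article never writes down a Group×Time test or a decision rule. It lists two factors and says differences will be measured. B2 versus B1 is one of those differences, it is the one the hypotheses point to, and a model with free group-by-time means estimates it without bias whether or not A is included. Contrasts and covariates are commonly left to the analysis plan. All of this stands. What remains is what the article does fix: the model it names as the efficacy test has Group A as a level, and nothing there limits efficacy to the randomised pair.

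Several stronger readings are tempting, and the documents do not support them:

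- **That the planned efficacy test has a 63–96% false-positive rate.** That range belongs to an inferred test, for ISI only, with the screening score reused as baseline. With a separate baseline and constant correlation there is no inflation. The other seven primary outcomes are not the selection variable, and no figure is available for them.
- **That including A biases the randomised estimate.** It does not; the B2-versus-B1 error rate stays near 5%.
- **That treating baseline as a TIME level is an error.** Difference in change is unbiased under randomisation; the covariate buys precision only.
- **That the article claims A shows the natural course of insomnia.** It speaks of natural changes in sleep during pregnancy, which a no-insomnia cohort can describe.
- **That A's status is hidden.** Randomization and Intervention say plainly that only Group B is randomised; it is Study design that conflicts with them.

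**Conclusion.** The point holds in a limited form and should be fixed. The article assigns the efficacy test to a model that includes a non-randomised group selected on a primary outcome, without tying that test to B2 versus B1. Read as Group×Time plus within-group change, a significant ISI result need not mean that the intervention differs from placebo. How often this would happen ranges from no excess to most trials, depending on how baseline ISI is obtained and on correlations the article does not give.

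Two descriptions are wrong or too strong as written, whatever those assumptions. Group A is not an arm of a 1:1 randomised trial. Nor can it be the no-intervention comparator for women with ISI of 8 or more: both B subgroups receive digital sessions, and no untreated group with insomnia exists.

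**What to change.** - **Efficacy test.** State it as the B2−B1 contrast at follow-up 1 in randomised women. Take it from a mixed model of the post-baseline visits at which the endpoint is collected, with the baseline value of the same endpoint as covariate.
- **Group A.** Report it separately as a descriptive, non-randomised reference cohort. Say that no efficacy conclusion will be drawn from A-versus-B or within-group tests.
- **Study design.** Describe a two-arm 1:1 randomised trial plus a non-randomised cohort.
- **Screening.** Limit Group A's role to describing normal sleep change in pregnancy. Say whether the screening ISI is also the baseline ISI.

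The cost is wording in the analysis and design sections; no new data are needed. The change also makes visible that the efficacy comparison rests on 76 women. At 38 per arm and two-sided 5%, an unadjusted comparison has 80% power for a standardised difference of about 0.65 and 59% power for 0.5. The rewording does not cause that limit, and the baseline covariate recovers some precision.
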